# ADVERSE EVENT REPORTING

The methods for collecting and reporting adverse events are described below.

#### Definitions

The definitions of adverse events (AEs), adverse reactions (ARs), serious adverse events/reactions (SAEs/ARs) andsuspected unexpected serious adverse reaction (SUSAR) are given below. It is of the most importance that all staff involved in the study is familiar with the content of this section. The principal investigator is responsible for ensuring this.

Adverse event and adverse reaction

An adverse event (AE) is the development of an undesirable medical condition or the deterioration of a pre-existing medical condition following or during exposure to a pharmaceutical product, whether or not considered causally related to the product. An undesirable medical condition can be:

- Symptoms (e.g., nausea, chest pain)
- Signs (e.g., tachycardia, enlarged liver)
- Abnormal test results of an investigation (e.g., laboratory findings, electrocardiogram).

In clinical studies, an AE can include an undesirable medical condition occurring at any time.

If any causality between the AE and the investigational drug is expected the AE is termed an adverse reaction (AR).

Serious adverse event and serious adverse reaction

A serious adverse event or reaction (SAE/SAR) is an adverse event or adverse reaction occurring during any study phase and at any dose of the investigational product, comparator or placebo, fulfilling one or more of the following criteria:

- Results in death
- Is immediately life-threatening
- Requires in-patient hospitalisation or prolongation of existing hospitalisation
- Results in persistent or significant disability or incapacity
- Is a congenital abnormality or birth defect

The causality of serious adverse events (i.e. their relationship to study treatment) will be assessed by the investigator(s), who in completing the relevant case report form must answer “yes” or “no” to the question: “Do you consider that there is a reasonable possibility that the event may have been caused by any of the following: – study medication? – other medication”?

**Suspected Unexpected Serious Adverse Reaction**

A suspected unexpected serious adverse reaction (SUSAR) is a serious adverse reaction with likely relationship to study treatment, which could not be expected from previous information of the investigational drug as described in the summary of the product characteristics.

#### Recording of adverse events

Information about adverse events will be collected from the first administration of any investigational product until the end of the study. Adverse events spontaneously reported by the patient and/or in response to an open question “have you had any health problems during the study since previous visit” from the study personnel or revealed by observation will be recorded at each visit from the first administration of any investigational product until the end of the study.

Any deterioration in laboratory values and vital signs need not be reported as AEs. However, abnormal values that meet criteria for an SAE or cause discontinuation of investigational product must be reported as SAE or AE and recorded in the CRF.

The time/date when the AE started and disappeared, maximum intensity, action taken with regard to investigational product, causality rating (yes or no), outcome, if AE caused patient to discontinue the study and whether or not it constitutes an SAE will be reported in the CRF for each AE.

The causality of non-serious AEs (i.e., their relationship to investigational product) will be assessed in the same way as for SAEs.

The intensity rating is defined as:

1 = mild (awareness of sign or symptom, but easily tolerated)

2 = moderate (discomfort sufficient to cause interference with normal activities)

3 = severe (incapacitating, with inability to perform normal activities)

It is important to distinguish between serious and severe AEs. Severity is a measure of intensity whereas seriousness is defined by the criteria as described above. An AE of severe intensity need not necessarily be considered serious. For example, nausea that persists for several hours may be considered severe nausea, but not a SAE.

Any AE not resolved at the last assessment or discontinuation of the study will be followed up within two weeks and thereafter as long as the investigator consider necessary.

The same parameters as for AEs / SAEs will be recorded in the case a SUSAR should occur during the study period.

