**SCHEDULE OF ACTIVITIES**

| **Protocol Activity** | Screen  **Day**  **-28 to -7** | Day 1 | Day 4 | Day 7 | Day 11 | Day 14 | Day 17 | End of Treatment and follow up  **Day 21 + 14 j** | Day 21 + 14 and 7 days forward |
| --- | --- | --- | --- | --- | --- | --- | --- | --- | --- |
| Informed Consent | X |  |  |  |  |  |  |  |  |
| Specific Medical History and Physical Examination | X |  |  |  |  |  |  |  |  |
| General Medical History and Physical Examination | X |  |  |  |  |  |  |  |  |
| Weight | X |  |  |  |  |  |  | X |  |
| Laboratory |  |  |  |  |  |  |  |  |  |
| Haematology | X |  |  |  |  |  |  | X |  |
| Blood Chemistry | X |  |  |  |  |  |  | X |  |
| Urinalysis | X |  |  |  |  |  |  | X |  |
| Coagulation | X |  |  |  |  |  |  | X |  |
| Pregnancy test a | X |  |  |  |  |  |  | X |  |
| ECG | X |  |  |  |  |  |  | X |  |
| Registration/Randomization | X |  |  |  |  |  |  |  |  |
| Study Treatment |  |  |  |  |  |  |  |  |  |
| Dosing pregabalin c |  | X --------------------------------------------------------------------------------- X | | | | | | | |
| Assessments |  |  |  |  |  |  |  |  |  |
| Skin | X | X |  |  |  |  |  | X |  |
| Muscle | X | X |  |  |  |  |  | X |  |
| Cold pressor test | Xd | X |  |  |  |  |  | X |  |
| Concomitant Medication e | X |  |  |  |  |  |  | X |  |
| Questionnaires |  |  |  |  |  |  |  |  |  |
| QOLQ f | X |  |  |  |  |  |  | X |  |
| mBPI-sf g | X |  |  |  |  |  |  | X |  |
| PD-Q h | X |  |  | X |  |  |  | X |  |
| PGIC i | X |  |  | X |  |  | X | X |  |
| Patient pain diary | X | X | X | X | X | X | X | X |  |
| Interview |  |  | X | X | X | X | X | X |  |

a Pregnancy tests will be done in females not postmenopausal for more than 1 year or sterilised.

c 75mg BID Day 1-3, 150mg BID day 4 – 7, 300mg BID Day 8 – 21 + 14 days followed by a 1 week medication taper, on half their maximum tolerated dose

d Cold pressor test training

e Concomitant medications will be assessed and noted at screening. Randomized patients will be advised to maintain their usual medication. As needs pain medication will be recorded in the diary.

f Quality of life Questionnaire

g Modified brief pain inventory-short form

h Pain DETECT questionnaire

i Patient Global Impression of Change. The PGIC questionnaire will be administered during outpatient clinic visits on Days 1 and Day 21+ 14 days and by telephone on days 7, and 17.

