## Endpoints

### Primary Endpoints

The primary endpoint for the study is analgesic effect of pregabalin therapy.

In the *clinical part* of the study, the primary efficacy parameter for analgesic effect is pain relief. This is defined as the reduction in VAS pain scores at the end of the study (day 21) as compared to the pre-treatment level. This effect is further assessed as changes in the daily experience of pain, which will be assessed using questionnaires, including the modified brief pain inventory-short form (mBPI-sf), the pain*DETECT* questionnaire (PD-Q, Freynhagen *et al*. 2006 [21]) and patient global impression of change (PGIC, Farrar *et al*. 2001 [22]).

In the *experimental part*, the primary endpoint for analgesic effect is change in pain processing. This is defined as the reduction pain tolerance thresholds in the dermatomes at the end of the study (day 21) as compared to the pre-treatment level. Pain processing will be assessed using QST parameters. All changes are compared to baseline recordings.

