# STUDY DESIGN

This will be a randomized, double-blind, parallel group, placebo-controlled study to investigate the effects of pregabalin on clinical and experimental pain in 60 patients with chronic pancreatitis (30 in Denmark and 30 in the Netherlands).

Participation in the study will involve three outpatient clinic visits, including the screening visit. The second and third outpatient clinic visit will include skin and muscle sensitivity testing. In addition, all subjects will undertake five telephone interviews.

During the study, the patients will be randomized to receive placebo or pregabalin (Lyrica®). The maximum daily dose of pregabalin is 300 mg administered twice per day. Pregabalin is titrated in 2 steps: for the first 3 days 75mg BID is administered. From Day 4 to Day 7, 150 mg BID is administered. From Day 8 to Day 21, 300 mg BID is administered. At the end of the study, patients will undertake a medication taper and will take half their maximum tolerated daily dose of pregabalin for 7 days and then discontinue dosing.

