# STUDY TREATMENTS

Patients will take either placebo or pregabalin, 75mg BID for the first 3 days, 150 mg BID for the next 4 days followed by 300 mg BID from Day 8 to Day 21 +14 days. If a patient does not tolerate 300mg BID it will be acceptable for them to maintain 150mg BID for the remainder of the study, following discussion and guidance from the investigator.

Pregabalin and placebo will be presented as grey capsules, which should be taken with approximately 250 ml water.

In order to maintain the blind, all patients will take doses of drug or placebo twice a day. Doses should be taken between 07:00 and 10:00 and between 19:00 and 22:00 (i.e. at approximately 12 hourly intervals).

After the last day of the study, the patients will taper their medication as detailed below:

Taper medication will be dispensed together with all other study medication at Visit 2. Taper will be administered to subjects who discontinue the study early only if they have completed 4 or more days of study drug. Thus patients who are unable to escalate from 75mg BID will simply cease medication. For all other subjects, the tapering period is 7 days.

- Subjects who were taking 300 mg BID pregabalin will have their dose reduced to 150 mg BID.
- Subjects who were taking 150 mg BID pregabalin will receive 75 mg BID.

Subjects who were taking placebo will continue on matching placebo for 7 days.

The amount of investigational products that is dispensed and returned will be recorded in the patient specific Case Report Form (CRF) by the investigator(s). It is essential that designated study personnel account for all medication. All discrepancies between amounts of investigational products dispensed and returned must be recorded and explained.

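### Adverse-event collection ends with the study while the 7-day study-drug taper follows it, and no contact is scheduled at which new events in that week would be asked about

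*Protocol*

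**What the plan says.** Protocol section 8, Recording of adverse events, sets the window: "Information about adverse events will be collected from the first administration of any investigational product until the end of the study". The next sentence ties recording to contacts: events reported spontaneously, elicited by an open question or observed "will be recorded at each visit from the first administration of any investigational product until the end of the study". The same section adds a follow-up rule: "Any AE not resolved at the last assessment or discontinuation of the study will be followed up within two weeks".

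The protocol has no formal definition of the end of the study. The nearest is in section 2.2.1, where the clinical primary endpoint is set out: "This is defined as the reduction in VAS pain scores at the end of the study (day 21) as compared to the pre-treatment level". Footnote j of the Schedule of Activities allows treatment to run up to 14 days longer for logistical reasons, so the last treatment day lies between day 21 and day 35.

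Section 5 places the taper: "After the last day of the study, the patients will taper their medication as detailed below". On its length it says "For all other subjects, the tapering period is 7 days"; the only exception is patients who could not escalate from the first dose step. Early discontinuers also taper if they had at least 4 days of study drug. Section 3 describes the same taper as dosing: "patients will undertake a medication taper and will take half their maximum tolerated daily dose of pregabalin for 7 days and then discontinue dosing". Patients on placebo continue matching placebo.

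The Schedule of Activities includes the taper in its footnote on dosing and has a last column headed "Day 21 + 14 and 7 days forward". No visit, interview, questionnaire or laboratory test is marked in that column.

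**The concern.** The taper is dosing with study drug, followed by stopping it. An event that begins then is an event on or just after exposure, and section 8's own definition of an adverse event covers conditions arising during or following exposure. Yet the collection window in the same section ends at a point that section 5 places before the taper.

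Safety and tolerability are stated objectives (section 2.1), and tolerability is to be compared with placebo (section 2.2.2). If nobody is asked about the taper week, that comparison and the end-of-study report of all adverse events describe only part of the regimen. What does reach the file for that week would depend on who happens to report.

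**Working it through.** The protocol gives no figure for adverse-event coverage, so there is none to reproduce. The check has two parts: a comparison of the relevant places, and the share of dosing days concerned.

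**1. Which contacts could pick up an event that starts in the taper?**

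| Place in the protocol | What it provides | Reaches new taper events? |
| --- | --- | --- |
| Section 6.2, telephone interviews | Calls on days 4, 7, 11, 14 and 17 about adverse events | No, all precede the taper |
| Section 6.2, final visit | Day 21, up to 14 days later; the taper instruction is given here | No, the taper starts afterwards |
| Section 3 | Three clinic visits and five calls in total | Leaves no further contact |
| Schedule, last column | Nothing marked | No |
| Section 8, two-week follow-up | Events unresolved at the last assessment or at discontinuation | No, only events already open |
| Schedule, footnote j | Excess medication may be returned at a later clinic visit | No adverse-event assessment attached |
| Section 8, spontaneous reports | Accepted, but recorded at visits and within the window | Only in part |

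**2. Share of dosing days.**

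Inputs: taper of 7 days (section 5); treatment of 21 days, extendable to 35 (Schedule, footnote j); early discontinuers taper after 4 or more days (section 5).

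Formula: share = taper days / (treatment days + taper days).

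- 21 days of treatment: 7 / (21 + 7) = 7/28 = 25.0%
- 35 days of treatment: 7 / (35 + 7) = 7/42 = 16.7%
- Early discontinuer after 7 days: 7 / (7 + 7) = 50%
- Early discontinuer after 4 days: 7 / (4 + 7) = 7/11 = 64%

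**3. The same share by drug quantity**, for a patient on pregabalin who reaches the highest step and follows the section 5 schedule. Daily totals are 150 mg for 3 days, 300 mg for 4 days, then 600 mg; the taper is 300 mg daily for 7 days.

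- 21 days: 450 + 1,200 + 600 × 14 = 10,050 mg; taper 300 × 7 = 2,100 mg; 2,100 / 12,150 = 17%
- 35 days: 450 + 1,200 + 600 × 28 = 18,450 mg; taper 2,100 mg; 2,100 / 20,550 = 10%

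If collection ran to the last taper dose, the window for completers would be 28 to 42 days instead of 21 to 35, and no dosing day would fall outside it.

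**The case against.** The strongest reply is that the end of the study is never defined for safety purposes. The day-21 figure comes from an efficacy definition, and the placement of the taper after the last study day may be loose drafting. The schedule counts the taper as dosing and gives the following week a column, and section 3 describes the taper as part of the design. On that reading the window already includes the taper. This stands as far as it goes: exclusion of the taper is the plain reading, not the only one. It does not remove the problem, because on the wider reading there is still no contact at which the events would be asked about.

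A reader might also infer that events in the taper, serious ones included, go uncaptured altogether. The documents do not support that. Section 8 accepts spontaneous reports, defines serious events as those in any study phase and at any dose, and requires immediate notification of serious events in the course of the study. If the taper counts as part of the study, a serious event reported then must be notified. What can be said is that new events are not solicited, and that the terms used for serious and unexpected events (the course of the study, the study period) carry the same ambiguity. Nor is it true that no patient is contacted after the final visit: those with open events are followed up within two weeks, and some may return medication later. Neither contact is systematic.

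Finally, the consequence is limited. The safety analysis is descriptive only (section 9, Safety Analysis), and the primary endpoint and its power are untouched. That is right, and it keeps this a recommended correction rather than an essential one.

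**Conclusion.** The point holds in this form. The adverse-event window in section 8, the taper in section 5 and the empty last column of the schedule do not fit together. On the plain reading the taper is outside the window; on any reading no scheduled contact solicits new events during the taper or on stopping.

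For patients who complete 21 to 35 days, the taper is 25% to 17% of dosing days. It should not be read as the share of events missed or of safety information lost: it counts days, the taper is at half dose, and by quantity the share is 17% to 10% under the assumptions shown above. It also does not describe everyone. Early discontinuers who taper have a larger share, and patients who stop without a taper have none.

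The conclusion assumes that the only scheduled contacts are those listed in section 6.2 and the schedule. Nothing in the text shows that the two-week follow-up was meant to cover new taper events, and the conclusion does not depend on what was intended.

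**What to change.** - In section 8, Recording of adverse events, state that adverse events and serious adverse events are collected from the first dose through the end of the 7-day taper, including for early discontinuers who taper.
- Align the sections on reporting serious adverse events and unexpected serious reactions, so that the course of the study and the study period have the same end point.
- Reconcile the wording in sections 2.2.1, 3 and 5 on where the study ends relative to the taper.
- In the Schedule of Activities, mark one telephone adverse-event interview in the existing last column, and change the count of calls in section 3 from five to six. Give early discontinuers who taper the same call at the end of their taper.

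No dose or clinical rule changes. The cost is one extra call per patient by the nurse or doctor who already makes five, plus the edits to wording. Onset dates are already recorded in the CRF, so events in the taper can be tabulated separately from those during treatment.

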#### Reporting of serious adverse events / averse reactions

Investigators and other site personnel must immediately inform sponsor of any SAE / SAR that occurs in the course of the study. The sponsor reports all SAEs / SARs to the Regulatory Authority and the Independent Ethics Committee once a year together with a security report.

Follow-up information on SAEs / SARs must also be reported by the investigator to the sponsor.

If a non-serious AE becomes serious, this and other relevant follow-up information must also be provided to sponsor as described above. All SAEs / SARs will be recorded in the CRF.

#### Reporting of suspected unexpected serious adverse reactions

In the case a SUSAR should occur during the study period the investigator and/or sponsor are responsible for informing the Regulatory Authority immediately and within 7 days for SUSARS resulting in death or causing life threatening conditions. All other SUSARs must be reported within 15 days. Appropriate follow up information must be reported within 8 days from the primary report. Reports will be reported electronically directly to the Regulatory Authority. Pfizer will be informed of eventual SUSARs as well. All SUSARs are recorded in the CRF.

- 1. **Reports at the end of the study**

At the end of the study, sponsor will report all AEs, SAEs, SARs and SUSARs in a final report for the Regulatory Authority and the Independent Ethics Committee.

**9.1.2 Experimental Study**

The experimental branch also includes 60 patients. The reliability and sensitivity of the described experimental tests are excellent (Staahl *et al*. 2006b [31]) Historically, 15-20 patients have been sufficient to reveal the effect of strong analgesics (Staahl & Drewes 2004 [32]). This was proven in a recent study where different opioids were tested in patients with chronic pancreatitis (Staahl *et al*. 2007 [33]). Based on a recent study (Buscher *et al*. 2006), typical chronic pancreatitis patients show a pain VAS of 4.4 cm (SD=2.4 cm) [34]. Based on these data, a group size of N=28 pancreatitis patients has sufficient statistical power (α=0.05, β=80%) to detect a clinically significant decrease of 2 cm in pain VAS due to treatment.

### Analysis of Primary Endpoint

All participants who have received the study medication for at least 2 weeks will be included in the analyses. Dropouts are replaced and excluded from further analyses.

All endpoints are described and presented graphically. Primary endpoints will be subjected to analysis of covariance (ANCOVA), to permit analysis of confounding variables to be included. Effect of the active treatment is evaluated and presented with 95% confidence intervals.

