### Secondary Endpoints

Secondary efficacy parameters are changes in quality of life compared to baseline level. The European Organization for research and treatment of cancer quality of life questionnaire (QOLQ, Bloechle *et al.* 1995 [23], will be used. Also the tolerability of the drug in this patient population will be compared to placebo.

In the experimental part of the study the difference of the QST stimulus are considered secondary efficacy parameters. The experimental baseline recordings will also be compared to published normal values from healthy controls to evaluate general aspects of pain processing in the patient group.

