## Screening

Visit 1; Screening (28 – 7 days before the first dose of study drug):

- Obtain informed consent.
- Physical examination.
- General and specific medical history (including drug/alcohol/tobacco consumption).
- Concomitant medication.
- Questionnaires (QOLQ, mBPI-sf, PD-Q and PGIC) are filled out.
- Blood and urine for hematology, clinical chemistry and urinalysis.
- Pregnancy test (urine) will be done in females not postmenopausal for more than 1 year or not sterile.
- 12-lead ECG.
- Blood pressure and pulse rate (supine and standing). Supine BP/PR should be measured following resting for 5 minutes. Standing BP/PR should be measured following standing for 2 minutes.
- Diary instruction. The patient will start completing the pain diary 7 days prior to the first dose of study drug.
- Experimental testing (training): pressure and electrical stimulation (skin and muscle) as described below.
- Cold pressor test (training) as described below.

Patients fulfilling inclusion and exclusion criteria are randomized and invited to join the study.

The duration time of the first visit will be approximately 4 hours.

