## Study Period

Seven days prior to the first dose of study drug, the patients will start to score pain levels in a pain diary. The average pain over the previous 24 hours and the worst pain over the previous 24 hours will be assessed using the VAS score. Usage of pain medication will also be recorded in the diary

Visit 2:

Day 1, first dose of study drug:

The patients visit the clinic and are instructed to start the trial medication if laboratory tests are normal. Ahead of the first dose of study drug the patients will undergo multimodal testing. They will have the skin in segments C5, T4, T10, L1 and L4 stimulated electrically. Also deep muscle pain will be assessed on the same places, using pressure stimulation. A cold pressor test is performed on the right hand and the deep muscle pain is measured on the left thigh both before and after the cold pressor test. Pain thresholds will be assessed using visual analogue scales (VAS).

These assessments are done before starting the treatment on Day 1 and on Day 21 + 14 days.

Patients will start the trial medication and score pain levels in the diary with a VAS value for the average pain over the previous 24 hours and a second VAS value for the worst pain over the previous 24 hours. Use of as needs pain medication will also be recorded in the diary.

The duration time of the second visit will be approximately 2 hours.

Telephone interviews

On days 4, 7, 11, 14 and 17 a study nurse or doctor will call the patients to assess the severity and tolerability of any adverse events.

On Day 7 a study nurse or doctor will call the patients to assess the adverse events and to administer the PD-Q and PGIC questionnaires. The dose of study drug will be discussed. Patients with acceptable adverse events will increase the dose to 300 mg BID. Patients experiencing unacceptable adverse events on 150 mg BID will be taken out of the study and will be replaced.

Visit 2:

All patients will visit the centre on day 21 + 14 days.

- Physical examination.
- Concomitant medication
- Questionnaires (QOLQ, mBPI-sf, PD-Q and PGIC) are filled out.
- Blood and urine for haematology, clinical chemistry and urinalysis.
- Pregnancy test (urine) will be done in females not postmenopausal for more than 1 year or not sterile.
- Experimental testing as described in visit 1: pressure and electrical stimulation (skin and muscle).
- Cold pressor test.

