## Subject Withdrawal

If unacceptable adverse effects are experienced by the patient between the telephone calls, the patient should contact the investigator. Based on a medical judgment, the dose of study drug may be reduced and the treatment continued or the patient may be withdrawn from the study. Follow up consultations and eventually additional blood tests will be arranged as by request judged by the investigator. The minimum end dose will be 150 mg BID, otherwise the subject will be withdrawn. Withdrawn patients or dropouts will be replaced until a number of 60 patients have fulfilled the study.

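### The primary efficacy analysis is limited to patients with at least 2 weeks of medication and leaves out dropouts, so it does not compare the arms as randomised

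*Protocol*

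**What the plan says.** The protocol fixes the analysis population in Analysis of Primary Endpoint: "All participants who have received the study medication for at least 2 weeks will be included in the analyses". The next sentence is: "Dropouts are replaced and excluded from further analyses".

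Other sections determine who becomes a dropout. At the Day 7 call (Study Period): "Patients experiencing unacceptable adverse events on 150 mg BID will be taken out of the study and will be replaced". Subject Withdrawal adds: "The minimum end dose will be 150 mg BID, otherwise the subject will be withdrawn". It also sets the replacement rule: "Withdrawn patients or dropouts will be replaced until a number of 60 patients have fulfilled the study". Study Treatments lets a patient who cannot tolerate 300 mg BID stay on 150 mg BID, while those who cannot move up from 75 mg BID stop medication.

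Secondary Endpoints includes tolerability: "Also the tolerability of the drug in this patient population will be compared to placebo". Neither Analysis of Secondary Endpoints nor Safety Analysis names a population for it. The protocol defines no all-randomised or all-treated set.

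**The concern.** Study Design describes a randomised, double-blind, placebo-controlled comparison. The analysis rule then conditions that comparison on staying on drug, which is a post-randomisation outcome that treatment can influence. Patients on pregabalin may leave because of adverse events and patients on placebo for other reasons, so those who remain in the two arms need not be alike. The planned ANCOVA adjusts for measured covariates and cannot restore the lost comparability. Replacement refills the headcount, not the randomised groups.

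At stake is the headline result: it would describe patients who stayed on treatment, not those who were started on it. A rule that is unclear for late leavers also leaves room for a choice after the data have been seen.

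**Working it through.** **1. Who is analysed**

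- Removed at the Day 7 call for adverse events on 150 mg BID: about a week of drug at most, so excluded by both sentences, and replaced.
- Unable to move up from 75 mg BID: stops in the first days, excluded by both sentences.
- Unable to tolerate 300 mg BID but continuing on 150 mg BID: stays in.
- Stops on Day 16: more than 14 days of drug, so included by the first sentence; a dropout, so excluded by the second.

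Early intolerance therefore always removes a patient from the efficacy set. For late leavers the text does not settle the matter.

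**2. Headcount**

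Inputs: 25% dropout, 48 completers and 60 recruited (Sample Size Determination, Clinical Study); 60 completers by replacement (Subject Selection, Subject Withdrawal).

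- The protocol's own figure: 60 is 48 × 1.25. Dividing by the retained share gives 48/0.75 = 64, and 60 recruited would leave 60 × 0.75 = 45.
- Under the replacement rule: 60/0.75 = 80 randomised, of whom 80 − 60 = 20, one in four, are left out. This counts every dropout as excluded; if late leavers are kept, fewer are lost.

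The two targets, 48 and 60 completers, also need reconciling.

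**3. When exclusion biases the contrast**

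Let d be the share dropping out of an arm and g the mean pain relief in its completers minus that in its dropouts. The completer mean exceeds the all-randomised mean by d × g, so

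completer contrast − all-randomised contrast = d(active) × g(active) − d(placebo) × g(placebo).

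Assumed cases, with no true effect among all randomised, SD 30, 30 analysed per arm and a two-sided 5% test, so SE = 30 × √(2/30) = 7.75:

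| Dropout, active / placebo | Gap, active / placebo | Bias | Rejection rate |
|---|---|---|---|
| 25% / 25% | 20 / 20 | 0 | 0.050 |
| 30% / 20% | 20 / 20 | 6 − 4 = 2 | 0.058 |
| 30% / 20% | 20 / 0 | 6 | 0.121 |
| 40% / 10% | 25 / 0 | 10 | 0.252 |

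If the second row is reversed (20% active, 30% placebo), the bias is 4 − 6 = −2, against pregabalin. The dropout splits and gaps are assumptions; the protocol gives only the overall 25%.

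**4. A severe illustration**

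Suppose dropouts have zero change, each arm loses 25%, and completers differ by D = 25. The protocol gives D no unit; it is read here as VAS points on 0–100. With placebo response r, the all-randomised difference is 0.75 × (25 + r) − 0.75 × r = 0.75 × 25 = 18.75, whatever r is.

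**5. Power if the effect is diluted in this way**

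Exact two-sided t test, alpha 0.05, SD held at 30. For D = 25, power at 24 per arm is 0.807; the protocol's table states 0.965, which is a separate problem and is not relied on here. For 18.75, power is 0.563 at 24 per arm, 0.663 at 30 and 0.788 at 40.

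**The case against.** Four stronger readings are tempting, and the protocol does not support them.

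*Tolerability is assessed only in those who tolerate the drug.* The exclusion sentence sits under the primary endpoint. Recording of adverse events collects events from the first dose and notes whether each led to discontinuation, the final report covers all adverse events, and Safety Analysis restricts no population. Tables of all dosed patients are not forbidden. What stands is that the set for the comparison with placebo is not stated, and that the exclusion, read literally, has no exception. Nor does the efficacy set hold only full tolerators: patients on 150 mg BID stay in, and those who leave for other reasons are also lost.

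*Randomisation precedes the laboratory results.* Screening says "Patients fulfilling inclusion and exclusion criteria are randomized and invited to join the study", and Study Period has patients "instructed to start the trial medication if laboratory tests are normal" on Day 1. But Randomization Criteria requires all entry criteria to be met, two exclusion criteria rest on laboratory values, and the Schedule of Activities places the only pre-dose blood tests at screening. Results may well be known before randomisation. Losses before the first dose under a blind are in any case not caused by the drug.

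*The effect is overstated by one third to one half.* The one third is 25/18.75 = 1.33. The one half needs 30% against 20% dropout with a placebo response of 10: 0.70 × 35 − 0.80 × 10 = 16.5, and 25/16.5 = 1.52. Both assume zero change in every dropout and compare two different target effects; neither is a measured bias.

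*Replacement itself breaks the comparison.* It does not, provided that replaced patients stay in the analysis.

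On the two sentences, it is fair to say that the first may define the set and that dropouts may mean those who fail it. That makes the Day 16 case an ambiguity, not a flat contradiction.

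**Conclusion.** The point holds for the primary efficacy analysis. The protocol states the rule outright, so this is not a detail left to a later analysis plan: inclusion depends on post-randomisation events that pregabalin can cause. The firm figure is the headcount, about 20 of 80 randomised patients left out, which rests on the protocol's 25% dropout, its target of 60 completers and the reading that all dropouts are excluded.

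The bias cannot be sized from the document. It is zero when dropout and the outcome gap are equal in both arms, and it can run either way. The assumed cases above give 0 to 10 points in favour of pregabalin and rejection rates of about 5% to 25% under no effect. The fall from 25 to 18.75 is illustrative only.

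Two lesser points also stand: the rule needs clarifying for patients who stop after two weeks, and the tolerability comparison needs a stated set.

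**What to change.** 1. Define the primary efficacy set as all randomised patients who took at least one dose, in their randomised arm, with no exclusion for duration or dropout. For the clinical endpoint, analyse the diary VAS scores up to withdrawal in a mixed model, attempt the final visit after early stopping where possible, and add a sensitivity analysis giving adverse-event dropouts no benefit. Keep the two-week set as supportive, and say which side of the line a patient who stops after two weeks falls.
2. State that tolerability and safety use all dosed patients, and count withdrawals for adverse events by arm.
3. If patients are replaced, keep the replaced patients in the analysis.

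No dose or withdrawal rule needs to change, and neither does the timing of randomisation.

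Cost: mainly protocol wording and some missing-data modelling. The estimate may be more conservative, and under a no-benefit assumption power is lower (step 5). The diary supplies data only up to withdrawal, so final visits after early stopping are extra work. The mixed model assumes that data are missing at random and would not in general return 18.75; the sensitivity analysis tests that assumption for adverse-event dropouts. The experimental endpoint is measured only before treatment on Day 1 and at the final visit, so it gains only where that visit is obtained.
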